**Outcomes in patient subpopulations**
• Assessment of treatment use and clinical outcomes among patients with:
◦ Traditional HCC risk factors, such as hepatitis B or hepatitis C virus infection (or co-infection), alcoholic liver disease, or cirrhosis
◦ Diabetes or multiple metabolic disorder
◦ HIV co-infection
• Assessment of the impact of underlying disease management on clinical outcomes in these patients
• Evaluation of potential regional/provincial differences in outcomes among patient subpopulations
**Impact of HCC screening**
• Assessment of influence of screening on:
◦ Treatment allocation and clinical outcomes
◦ Overall survival
◦ Underlying disease
• Evaluation of the cost-effectiveness of mandatory HCC screening
**Health care access**
• Evaluation of the level of health care access in different regions/provinces and association with clinical outcomes
• Examination of any potential influence of immigrant/minority status, risk factor status, and alcohol and drug use on health care access

### Loss to follow-up

Throughout the HCC BRIDGE China national study, patients are expected to leave via loss to follow-up, by consenting to enter a randomized clinical trial of primary HCC treatment, or at death. Death certificate searches or interviews with the patient's caregiver, relative, or health care provider will be used to verify deaths. The inability to verify deaths is expected for 5% of patients in the study. Sample size calculations have been adjusted accordingly to account for this level of missing data for the primary end point of the study.

## Results

The number of patients enrolled across the various geographic regions captured in the global HCC BRIDGE study is expected to exceed 20,000. For the HCC BRIDGE China national study, a total of 15 sites across China have been selected for inclusion at the time of writing. At present, the anticipated country-wide study population is approximately 9000 patients (Figure 1).

**Figure 1 F1:**
[figure not shown]
**Geographic distribution of sites currently included in the HCC BRIDGE China national study**.

## Discussion

Over the past 3 to 4 decades, China has experienced a substantial increase in the incidence of HCC [5], and the country now accounts for more than half of the world's cases of this malignancy [2,3]. Nevertheless, in spite of the huge health care burden of HCC in China, there has never been a truly geographically representative study of HCC in this country and active surveillance is currently lacking. This suggests that the current estimates of the incidence and prevalence of HCC in China may not be accurate, and that regions with a current high unmet need and/or a high risk for new HCC cases may be unidentified.

The HCC BRIDGE China national study is the first geographically representative epidemiologic study of HCC in China and is expected to include more than 9000 patients over its course. This study, via its inclusion of a large number of sites across all 7 traditional regions of China, will facilitate a thorough assessment of HCC patient characteristics, treatment allocation, and clinical outcomes, across the entire country, as well as allowing a unique analysis of possible regional variations in these aspects of HCC epidemiology and management. Ultimately, the study will help determine levels of unmet medical need and identify regions of high risk for HCC within China.

As well as contributing to the general understanding of treatment patterns and associated outcomes among HCC patients in China, the data generated by the HCC BRIDGE China national study may provide insights into other aspects of HCC epidemiology and management, such as the potential role of HCC screening in treatment allocation and outcomes, and possible differences in clinical outcomes among different HCC patient subpopulations. Moreover, the study data may further help address other unanswered questions related to HCC in China, including questions about the appropriateness of current standards of care for HCC, the extent of usage and the impact of traditional Chinese herbal medicine, and best practices in clinical care for Chinese patients with HCC. Through these investigations and analyses, the study also has the potential to inform ongoing China public health reform, policy, and practice.

The eventual findings of the HCC BRIDGE China national study will need to be considered in light of the study's strengths and weaknesses. The primary strengths of this study are (1) the large number of patients included; (2) the geographic representativeness of the included sites; and (3) the use of real-life clinical practice data. Additional strengths include the use of centralized data monitoring, cleaning, site queries, and checking of invalid clinical values, which will enhance the quality of the collected data, as well as the use of identified prognostic factors for HCC survival to control for population differences that may influence treatment outcomes. The main potential study limitations are (1) treatment comparisons are performed in patients without prospective randomization methodology; (2) both academic and nonacademic centers/hospitals are included, which may result in differing quality of medical care for enrolled patients; (3) data quality is dependent on the thoroughness of the clinician's documentation of medical history, treatment, and outcomes; and (4) data collection bias is possible since clinical assessments are not conducted at predefined time points, as in a clinical trial, but at times determined by clinicians and their patients.

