### Patients

All patients enrolled in the HCC BRIDGE study must meet 3 key inclusion criteria: (1) diagnosed with HCC between January 1, 2005, and June 30, 2011, in accordance with American Association for the Study of Liver Diseases/European Association for the Study of the Liver guidelines [11]; (2) aged at least 18 years at the time of HCC diagnosis; and (3) received or receiving treatment for HCC through a site enrolled in the HCC BRIDGE trial. Patients participating in other clinical trials will be included in the study if the patient is enrolled in a single-arm clinical trial, enrolled in a randomized clinical trial of HCC adjuvant therapy, or was not selected to receive active treatment in a randomized clinical trial that was conducted between 2005 and 2007. Any patient whose first active HCC-directed treatment is received via participation in a randomized clinical trial of primary HCC therapy will be excluded from the current study, since this treatment regimen would have been determined by a study protocol rather than by the treating physician. Similarly, patients included in the China national study who subsequently enroll in such a trial will be censored from the study at that time point. Patients with unknown month and year of HCC diagnosis or of the first visit at the site of inclusion will be excluded. Furthermore, to preserve regional representation within China, patients who reside outside the province of interest for a particular study site will also be excluded. Finally, in order to avoid selection bias when the number of eligible patients at a site exceeds the number allowed according to study sample size calculations, an enrollment scheme will be adopted such that the same number of consecutive patients are enrolled each month. For example, in the first year of data entry, if a site is to enroll 200 patients, approximately 17 consecutive patients diagnosed with HCC will be enrolled in each month. If there are less than the specified numbers of patients in any given month, we ask that the corresponding number of extra patients be enrolled in the following month.

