### Sample size

Sample size requirements for the Chinese regional sites are approximately 200 patients per site per year between 2008 and 2010 (plus approximately 192 per site for the first 6 months of 2011) to capture current treatment and clinical outcomes in HCC, and 100 patients per site between 2005 and 2007 for historic controls. Pooling of data across all sites in China will be employed to describe disease and treatment characteristics across the country.

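### The Discussion says the study will help identify regions of high HCC risk, but a capped cohort of treated cases without population denominators cannot show regional risk

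*Protocol article*

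**What the plan says.** The second paragraph of the Discussion closes by saying that the study will help gauge unmet need and "identify regions of high risk for HCC within China". The paragraph before it supplies the meaning of risk: because current incidence and prevalence estimates may be inaccurate, "regions with a current high unmet need and/or a high risk for new HCC cases may be unidentified".

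The design is set out in the Methods:

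- **Patients:** entry requires being "diagnosed with HCC between January 1, 2005, and June 30, 2011" and having "received or receiving treatment for HCC through a site enrolled in the HCC BRIDGE trial". Patients living outside the province of interest for a site are excluded.
- **Sample size:** the target is common to all sites: "approximately 200 patients per site per year between 2008 and 2010", "plus approximately 192 per site for the first 6 months of 2011", and 100 per site for the 2005 to 2007 historic controls.
- **Patients (enrolment scheme):** where a site has more eligible patients than its allowance, "the same number of consecutive patients are enrolled each month". A shortfall in one month is made up in the next.
- **Study sites:** sites are tertiary or oncology centers, and one criterion is that their mix of causes of HCC agrees with the national average.
- **Data collection:** every listed item concerns enrolled patients.

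**The concern.** To say that one region has a higher risk of HCC than another, one needs new cases over the population that could have become cases, or at least a numerator and denominator that can be compared between regions. The article describes neither. The numerator is limited by a recruitment target, and no denominator is listed. The claim is therefore a capability that the stated design does not have.

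What is at stake is interpretation. The Discussion offers the study as a response to inaccurate incidence and prevalence estimates, and the limitations listed there do not warn that regional risk is out of reach. A reader could take regional case counts from this cohort as evidence of where HCC is more common.

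**Working it through.** **1. What the plan's own figures give.** The article states no regional risk figure, so there is none to reproduce. Its only total is about 9000 patients at 15 sites, or 9000 / 15 = 600 per site. The per-site targets add up to 3 × 200 + 192 + 100 = 892, and 15 × 892 = 13,380. If the 100 historic controls are per year, the sum is 1,092 per site and 16,380 in all. Only the 2008 to 2010 target on its own gives 15 × 600 = 9000. That gap is a separate matter. It is used here only to show that full targets at every site cannot be assumed.

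**2. Numerator above the cap.** Enrolled cases are roughly min(target, eligible cases). For 2008 to 2010 the cap is 200 / 12 = 16.7 a month, which the article rounds to 17. The number of eligible cases per site is not given, so the values below are assumptions. Monthly arrivals were simulated as Poisson, with any shortfall carried forward within the year (5,000 simulated years per row).

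| Eligible cases a year (assumed) | Mean enrolled a year |
|---|---|
| 150 | 149.7 |
| 200 | 190.6 |
| 250 | 199.4 |
| 300 | 199.9 |
| 500 | 200.0 |
| 750 | 200.0 |
| 1000 | 200.0 |

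Between 250 and 1000 eligible cases the true ratio of volumes is 4.0, while the ratio of enrolled counts is 200.0 / 199.4 = 1.003. The threshold moves with the target. In the first half of 2011 it is 192 / 6 = 32 a month, so a site's count may also change between periods because the target changed.

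**3. Numerator below the cap.** Here enrolment follows eligible volume (150 gives about 150). Eligible volume at a site is

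eligible = I × N × s,

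where I is incidence in the source population, N is its size and s is the share of its cases treated at that site. Halving I and doubling s leaves the count unchanged. The provincial residence rule limits where patients come from, but supplies neither N nor s.

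**4. Denominator.** Suppose all 200 cases a year were the complete case load of their source population. The implied rate would be 200 / N:

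| N (assumed) | Cases per 100,000 a year |
|---|---|
| 1 million | 20 |
| 5 million | 4 |
| 20 million | 1 |
| 80 million | 0.25 |

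The range is 20 / 0.25 = 80-fold, and none of the data items listed narrows it.

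**5. Planned analyses.** The Data analysis section gives treatment use, patient characteristics, and age- and gender-adjusted rates of the study end points. Those rates are event rates among patients with HCC, not rates of HCC in a population. Table 2 adds regional differences in outcomes and in access to care, again among patients. Choosing sites whose causes of HCC resemble the national average also reduces whatever indirect signal the regional mix of risk factors might have carried.

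**The case against.** The strongest defence is that this is one loosely worded clause. It says the study will help, which is less than a promise of an estimate. It is absent from the two numbered purposes of the global study in the Background and from the Conclusion, and no end point, model or test rests on it. All of that is correct and limits the weight of the point. It does not rescue the clause, because nothing described supports even an informal ranking of regions by risk of new cases.

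It could also be said that an article condenses a fuller protocol. The point does not depend on an omission alone: case-only entry, a common target and the cap are all stated, and capped case counts cannot yield incidence by later analysis.

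Some stronger readings are tempting but not supported:

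- A reader might infer that regional counts depend only on how the 15 sites are spread over the 7 regions. The equal-monthly scheme applies only where eligible patients exceed the allowance, and below that counts follow site volume. Large differences in volume collapse to equality only if each site has more than about 200 eligible cases a year.
- A reader might infer that a map or ranking of high-risk regions is planned. None is. The sentence about informing public health policy follows a paragraph on screening, subpopulations, standards of care and herbal medicine.
- A reader might infer that the unmet-need half of the sentence fails as well. Access, treatment allocation and outcomes among treated patients can be compared across regions. Since treatment is an entry condition, patients who received none are not seen, which is a caveat on scope and not an error.

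**Conclusion.** The concern holds for the high-risk-regions clause alone. A cohort of treated cases at selected sites, with a common target, a cap and no listed population at risk, cannot identify regions where the risk of developing HCC is high. Regional case counts will reflect the number of sites, site volume, referral and the cap.

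Two figures indicate the size, and both rest on assumed inputs. Above about 200 eligible cases a year (2008 to 2010), a 4-fold difference in volume shrinks to a ratio of about 1.00. For 200 cases a year, source populations from 1 to 80 million imply rates that differ 80-fold. The conclusion itself depends on neither figure, only on the stated entry criteria, targets and data items.

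The consequence is confined to what the study may claim. The primary and secondary end points and the treatment comparisons are untouched.

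**What to change.** 1. In the Discussion, remove the clause on identifying regions of high risk.
2. In its place, state that regional comparisons describe case mix, treatment, access and outcome among treated patients at participating sites.
3. Add to the limitations in the Discussion that regional incidence or risk of HCC cannot be estimated, because only cases are enrolled, enrolment is capped per site, and no population denominator is collected.
4. As a caveat, note beside unmet medical need that it is assessed among treated patients only.

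These are wording changes. Data collection, sample size and analyses stay as they are. The price is a less favourable statement of what the study can show. Reporting each site's total of eligible cases before the cap would be an optional descriptive extra. The article does not say that such totals are recorded, so this could mean additional chart work, and the totals would still not be rates.

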## Conclusion

In conclusion, the HCC BRIDGE China national study represents the first geographically representative study of HCC in China and will contribute significantly to the understanding of patterns of HCC therapy use and related clinical outcomes, as well as knowledge of continuing unmet needs for HCC.

